## Abstract

**Background:**

Fifth metatarsal fractures are one of the most common foot fractures, and 11% to 25% of such fractures are Dancer’s fractures (distal spiral fractures). Conservative therapy while wearing a cast and operative treatment have been used as preferred modes of treatment in the limited literature available. However, we often see healing problems, such as delayed union and nonunion, when Dancer’s fractures are treated nonoperatively, resulting in a need for secondary intervention. In our institution, treatment has changed over the years from predominantly conservative treatment to mostly operative treatment. To investigate whether our hypothesis holds true that primary surgical treatment is beneficial, a retrospective study was designed.

**Objective:**

The objective of the study is to compare differences between outcomes (delayed union and nonunion) of conservative and operative treatments for Dancer’s fractures.

**Methods:**

A retrospective comparative cohort study will be conducted in a level II trauma center (Zaandam Medical Center). Patients who experienced a Dancer’s fracture in the period of 2012 to 2021 will be included and divided into 2 cohorts—the conservative (2012-2015) and operative (2016-2021) treatment cohorts. The primary outcome will be the differences in percentages of delayed union and nonunion between the two groups. The secondary outcomes will be the percentage of primary conservative treatment failure, the need for secondary operative treatment, complications (infection and hardware failure), and functional outcomes. If 118 patients are included in each group, sufficient power is expected to be reached, depending on the age distribution of patients. The percentages of delayed union and nonunion among the two groups will be calculated and statistically compared via chi-square statistics. A logistic regression analysis will be used to investigate possible associations between patient characteristics and failed conservative treatment. A Mann-Whitney *U* test will be used to compare functional outcomes between groups. An independent, 2-tailed *t* test will be used to compare mean 12-Item Short Form Survey scores if they are normally distributed, and a Wilcoxon rank sum test will be used if they are nonnormally distributed.

**Results:**

In total, 2134 potentially relevant health insurance codes have been extracted from the hospital’s register. We expect to find a total of 236 Dancer’s fractures in this data set.

**Conclusions:**

Our study has limitations due to it being a single-center study and data collection being performed retrospectively. However, it covers a large time period and may provide the possibility to show treatment outcome differences (delayed union and nonunion, complications, and functional outcomes) in 2 reasonably large cohorts (conservative and operative treatment cohorts), which has not been done before in literature on Dancer’s fractures. If our hypothesis that surgery is beneficial for Dancer’s fractures is proven true by our study, we plan to further corroborate it by conducting a prospective randomized controlled trial.

**International Registered Report Identifier (IRRID):**

PRR1-10.2196/37171

## Introduction

Fifth metatarsal fractures are one of the most common foot fractures [1,2]. There is no unified classification system; however, the Lawrence and Botte classification is recommended [3]. The fifth metatarsal bone is divided into 3 anatomical zones where fractures can occur. Zone 1 is the tuberosity; zone 2 is the metaphyseal-diaphyseal junction, which extends into the fourth-fifth intermetatarsal facet and is also known as the *Jones fracture*; and zone 3 consists of the proximal diaphyseal fractures, which are located within 1.5 cm of the tuberosity [4]. Another type of fracture is the so-called *Dancer’s fracture*—a long spiral fracture that extends into the distal metaphyseal area [4]. Dancer’s fractures are diagnosed in 11% to 25% of fifth metatarsal fractures [1,5,6] and 5% of metatarsal fractures overall [7]. The optimal treatment for this fracture type is still under debate, and most of the available related literature only consists of small retrospective studies or case series.

Studies have shown different outcomes of treatments. Some have used conservative therapy with or without weight-bearing immobilization for 6 to 8 weeks and achieved excellent results [6-10]. Others have used surgical therapy with plates and screws, which resulted in excellent outcomes [11,12] that were comparable to those of the same therapy for shaft fractures of other metatarsal bones [13]. Patient characteristics such as age and osteoporosis [5,14], as well as fracture characteristics such as the angulation of the fracture and comminution of the fragments, are important factors in the choice of treatment [15]. Dancer’s fractures are usually angulated and short [11]. It has been shown previously that dislocation is associated with functional impairment in patients with metatarsal fractures [2]. Therefore, malunion, delayed union, or nonunion is expected if Dancer’s fractures are treated nonoperatively. Due to advancing insights, from 2016 onward, the preferred treatment in our hospital changed from predominantly conservative treatment to mostly operative treatment. Our hypothesis is that Dancer’s fractures often result in healing problems, such as delayed union and nonunion, when treated nonoperatively.

The aim of our study is to compare outcomes of primary operative treatment for Dancer’s fractures to those of conservative treatment. It is hypothesized that primary operative treatment can be beneficial when it comes to reducing delayed union and nonunion rates.

## Methods

### Study Objectives

The primary objective is to provide an overview of all Dancer’s fractures, the applied initial treatments, and final outcomes—delayed union and nonunion rates and complications. The secondary objective is to determine how many fractures needed surgery after they were initially treated conservatively. The third objective is to identify associations between patient characteristics and failed initial conservative treatment. Finally, we will measure functional outcomes in both patient groups.

### Study Design and Setting

Our study will be a retrospective cohort study. The researchers will be provided with records and diagnostic health insurance codes by the hospital’s medical administration. These codes represent patients with foot injuries (codes 237 and 238 for metatarsal and tarsal fractures, respectively) over the past 10 years in a single, regional, level II trauma center—the Zaandam Medical Center, Zaandam. These cases will be retrospectively analyzed to select oblique diaphyseal fractures of the fifth metatarsal bone, which are known as *Dancer’s fractures*. Since 2016, in our hospital, the preferred treatment changed from predominantly conservative treatment to mostly operative treatment. Therefore, the comparison of 2 historic cohorts will be made—the conservative treatment cohort (2012-2015) versus the operative treatment cohort (2016-2021).

### Study Population

Patients aged ≥18 years who presented to the emergency department or outpatient clinic with a Dancer’s fracture within 48 hours after trauma will be considered eligible for participation in our study.

### Exclusion Criteria

Patients with multiple, simultaneous ipsilateral foot or ankle fractures; open fractures; known, pre-existing, significant impaired mobility; or any pretrauma, gross anatomical anomaly of the foot will be excluded from participation in our study.

### Recruitment

A list of all foot fracture–related diagnostic health insurance codes in the Zaandam Medical Center dating from 2012 to 2021 will be provided by the hospital’s medical administration. All corresponding radiographs of the foot will be reviewed by 2 trauma surgeons to identify Dancer’s fractures. Patient characteristics such as age and sex, as well as fracture characteristics such as comminution, dislocation, the side of injury, and the occurrence of delayed union and nonunion, will be extracted from the electronic patient records manually by the researcher. Delayed union and nonunion are defined as absent or incomplete fracture healing after 3 and 6 months, respectively, and they will be assessed by reviewing the radiographs. The given treatments (cast vs surgery) and occurrence of complications (infection and hardware failure) will also be extracted from the electronic patient records manually by the researcher. The cohort will be divided into the following two groups: the conservative treatment cohort (2012-2015) and operative treatment cohort (2016-2021).
Patients will receive a letter about providing informed consent. The letter will state that after they provide consent, a researcher will call them. Patients will be asked if they underwent secondary surgery in another hospital and be asked to provide data that are missing from the electronic patient files, such as the mechanism of injury and smoking status at the time of injury.

Patients will also be asked to complete the 12-Item Short Form Survey (SF-12) questionnaire and to rate their functional outcomes by using 1 of the following 3 categories: (1) no more complaints or pain, (2) minor complaints or pain without an impact on daily living, and (3) significant complaints or pain with an impact on daily living [16].

If patients are lost to follow up, it will be assumed that they did not experience delayed union, nonunion, or other complications.

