### Sample Size

Based on the limited available literature, delayed union and nonunion have been found in 3% to 9% [7,8] of patients in the general population who were treated nonoperatively. For patients aged ≥40 years, the delayed union rate for nonsurgical treatment is 35% [5]. This rate ranges from 4% to 7% for patients who were treated operatively [11,12]. It is expected that 236 patients will be included in our study, with approximately 118 in each cohort. Based on a post hoc power analysis, a power of 34.3% can be achieved by recruiting patients from the general population, and a power of 100% can be achieved by recruiting patients aged ≥40 years. As the incidence rates of delayed union and nonunion are unreliable in the available (limited) literature, the post hoc power analysis showed large differences in power—a problem that is often encountered [17]. However, our cohort will be the largest cohort of patients with Dancer’s fractures to date. Based on our clinical experience, we also believe that the incidence of delayed union and nonunion might be high in the nonoperative treatment cohort. The data collected in this study can be used to calculate the number of patients that need to be included in future prospective studies.

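### Case selection is not limited to the presenting radiograph, so inclusion of borderline fractures can depend on treatment or healing; the size of any bias is unknown and may be small

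*Protocol article*

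**What the plan says.** Recruitment describes how cases are found: a list of foot-fracture insurance codes is obtained, and then "All corresponding radiographs of the foot will be reviewed by 2 trauma surgeons to identify Dancer’s fractures". Study Design and Setting describes the same step: "These cases will be retrospectively analyzed to select oblique diaphyseal fractures of the fifth metatarsal bone". Neither sentence says which film decides the fracture type, or whether the surgeons may see later films at that point.

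The primary outcome comes from the same kind of material. Recruitment gives the definition: "Delayed union and nonunion are defined as absent or incomplete fracture healing after 3 and 6 months, respectively". On how these are judged, the same section adds "and they will be assessed by reviewing the radiographs". The researcher extracts treatment and the occurrence of delayed union and nonunion from the patient records.

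Study Population ties eligibility to early presentation: a patient "with a Dancer’s fracture within 48 hours after trauma will be considered eligible".

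The target fracture is not described uniformly. The Introduction calls it "a long spiral fracture that extends into the distal metaphyseal area", the Abstract calls it a distal spiral fracture, and Study Design and Setting proposes "to select oblique diaphyseal fractures of the fifth metatarsal bone".

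Sample Size records the investigators' expectation: "we also believe that the incidence of delayed union and nonunion might be high in the nonoperative treatment cohort". Strengths and Limitations does not mention case selection with later films in view.

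**The concern.** In a retrospective cohort, eligibility should be settled on what was known at presentation. If the reader who decides whether a fracture qualifies can also see a plate, or a fracture line still open at 3 or 6 months, a doubtful case can be let in or left out partly on its treatment or outcome. Differing case descriptions and a stated expectation about direction make this more plausible, though neither shows that it happens.

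At stake is the primary comparison of delayed union and nonunion rates. Selection of this kind changes both who is counted as an event and who is in the denominator. Regression on the selected patients cannot restore cases that were left out or identify those wrongly let in. Events may be few, so a handful of decisions could matter. The results are also meant to inform the sample size of a later randomized trial.

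**Working it through.** **Inputs from the article.** About 118 patients per cohort. Conservative event rates of 3% to 9% in the general population and 35% at age 40 or over; operative rates of 4% to 7% (Sample Size). Chi-square comparison (Statistical Analysis). Significance level and sidedness are not stated; two-sided 0.05 is assumed.

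**The plan's own figure.** With 9% versus 4% and n = 118 per cohort, the pooled-variance formula is

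power = Φ{[|p1 − p2|·√n − 1.96·√(2·p̄(1 − p̄))] / √(p1(1 − p1) + p2(1 − p2))}.

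Here p̄ = 0.065, so the numerator is 0.05 × √118 − 1.96 × √(2 × 0.065 × 0.935) = 0.543 − 0.683 = −0.140. The denominator is √(0.0819 + 0.0384) = 0.347. Φ(−0.404) = 0.343, which matches the stated 34.3%. For 35% versus 4% the result is 1.000, which matches the stated 100%. The power figures are not in dispute; they fix the test used below.

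**Illustration 1: unhealed conservative cases let in.** The assumptions are a true rate of 4% in both cohorts, and k extra conservative cases admitted, all of them unhealed. The article does not give k. The expected events are 118 × 0.04 = 4.72, so the apparent rate is (4.72 + k)/(118 + k). The rejection rate is the exact two-sided probability for the uncorrected Pearson chi-square. It is summed over two independent binomials (118, 0.04), with k certain events and k patients added to the conservative cohort.

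| k | Apparent conservative rate | Rejection rate |
|---|---|---|
| 0 | 4.0% | 4.4% |
| 2 | 6.72/120 = 5.6% | 6.9% |
| 4 | 8.72/122 = 7.1% | 14.6% |
| 6 | 10.72/124 = 8.6% | 29.5% |

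At k = 6 the added failures outnumber the 4.72 expected genuine ones, so that row is an extreme case.

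**Illustration 2: healed conservative cases left out.** Suppose healed conservative cases are missed with probability m and unhealed ones are always kept. The apparent rate is p/[p + (1 − p)(1 − m)]. With a true rate of 9% in both cohorts:

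- m = 10%: 0.09/(0.09 + 0.819) = 9.9%
- m = 20%: 0.09/(0.09 + 0.728) = 11.0%
- m = 30%: 0.09/(0.09 + 0.637) = 12.4%

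Putting these against 9% in the power formula gives a chance of a significant result favouring surgery of about 4.2%, 7.4% and 13.1%, against a nominal 2.5% in that direction. By this route, material inflation needs strong selection.

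**The case against.** A reader might infer that the article states outright that postoperative and follow-up films decide inclusion. It does not. The word corresponding refers to the insurance codes, and all may mean only that the whole list, about 2667 codes, is screened. Reading it as every film for each injury is natural but not spelled out.

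There is also evidence pointing the other way. Eligibility rests on presentation within 48 hours of trauma. Identification by the surgeons and extraction by the researcher are described as separate tasks. Fracture type concerns location and line, not union, and is normally visible on the first film. The investigators' expectation is a hypothesis about outcomes, not evidence of biased selection. A fuller protocol might contain a masking rule.

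Most of this stands, and it limits the point to a possibility. It does not remove it. The 48-hour rule dates the presentation but does not say which film settles the type. Separate tasks do not keep later films from the surgeons. The one instruction the article gives covers all corresponding films, without restriction.

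The illustrations are also one-sided. They add no healed conservative case and no operative case, although a plated fracture could equally be easier to include. They show sensitivity, not an expected error.

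**Conclusion.** The point holds as a weakness in a stated procedure. Case selection is not confined to the presenting film, later films in the same set can show treatment and union, and the fracture descriptions differ. Inclusion of borderline cases can therefore depend on treatment or healing.

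The bias is of unknown and possibly small size. Under the assumed one-sided selection at 4%, two added unhealed cases move the rejection rate only from 4.4% to 6.9%; four or six take it to about 15% or 29%. The number of borderline cases is an assumption throughout.

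Two stronger conclusions are not supported: that selection on the outcome will occur, and that it could never be examined later. Re-reading the presenting films in a sensitivity analysis would test it directly. Because prevention costs little, the change should still be made.

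**What to change.** State that the same two surgeons classify fracture type on the presenting (injury) radiographs only, and that the case list is locked before any follow-up or postoperative film or the chart is opened. Treatment and union are extracted afterwards. Use one written case definition; the descriptions in the Abstract, Introduction and Study Design and Setting must be reconciled, and the choice is the investigators'. Record disagreements and report agreement between the two surgeons.

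The cost is a changed order of film review and the work of locating the first film for each code. No additional patients are needed, and the power figures do not change. Hiding film date and patient identity would add protection, because the cohorts are calendar periods. It would take real effort across about 2667 codes and probably someone other than the two readers, so it is optional.

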### Comparison With Prior Work

Previous studies have looked at either nonoperative treatment [6-10] or operative treatment [11,12]. To our knowledge, no studies have compared operative treatment to nonoperative treatment before. We expect to find higher rates of delayed union and nonunion in older, female patients [5] and those who smoke, similar to previous findings in related literature. Patients with displaced fractures might benefit the most from surgical intervention, as suggested by Thompson et al [11].

Considering the knowledge gap in literature with regard to the optimal treatment of Dancer’s fractures, it is important to first gain insight into our hypothesis before applying for grants for a costly randomized controlled trial.

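### Baseline dislocation and comminution are to be taken from the patient record and not stated to be graded on the presenting radiograph, so their recording may differ by treatment and by conversion to surgery

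*Protocol article*

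**What the plan says.** The Recruitment section of the protocol article names a task and a source for each item.

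- **Case finding:** "All corresponding radiographs of the foot will be reviewed by 2 trauma surgeons to identify Dancer’s fractures". No other task is given to this review.
- **Fracture characteristics:** "fracture characteristics such as comminution, dislocation, the side of injury" are items that "will be extracted from the electronic patient records manually by the researcher". Delayed union and nonunion stand in the same list.
- **Outcome:** for delayed union and nonunion the next sentence adds that "they will be assessed by reviewing the radiographs". No such sentence covers comminution or dislocation, and neither is given a definition or threshold.

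Elsewhere the article gives these features weight. The Introduction says that "fracture characteristics such as the angulation of the fracture and comminution of the fragments, are important factors in the choice of treatment", and it links dislocation to functional impairment. Comparison With Prior Work, citing an earlier study, says: "Patients with displaced fractures might benefit the most from surgical intervention".

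**The concern.** By the protocol's own account, fracture severity influences who is operated on and may influence who benefits. Such a variable should be measured in the same way in every patient, without regard to what happened later.

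A patient record need not meet that condition. An operation normally brings a written indication and an operation report, both describing the fracture; a cast does not. In a patient converted from cast to surgery, the description may refer to the fracture at operation and not at presentation. Recording may therefore depend on treatment. Within the conservative group it may depend on conversion to surgery, which is how the Outcomes section defines failed conservative treatment.

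At stake are the description of the two cohorts by severity, any regression of conservative failure that includes dislocation or comminution, and any statement that displaced fractures gain most from surgery. Future Directions and Conclusions intend the findings to inform patient selection for a later randomised trial and decisions for individual patients. The Strengths and Limitations section mentions recall bias and non-standardised follow-up, but not this. The planned telephone call to patients cannot recover fracture geometry.

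**Working it through.** **Step 1. Sources side by side (Recruitment).**

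| Item | Who | Source stated |
|---|---|---|
| Dancer's fracture, yes or no | two trauma surgeons | all foot radiographs |
| Comminution, dislocation | the researcher | electronic patient record |
| Delayed union, nonunion | the researcher | electronic patient record, then expressly radiographs |

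The natural reading is that image review was specified for case finding and outcome, but not for baseline severity.

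**Step 2. The protocol's own figures.** The protocol gives no figure on this point. Its power figures (Sample Size) do not use these variables. The 34.3% reproduces with 118 per cohort, 9% versus 4%, and an assumed two-sided alpha of 0.05:

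- SE under the null = √(2 × 0.065 × 0.935 / 118) = 0.0321
- SE under the alternative = √((0.09 × 0.91 + 0.04 × 0.96) / 118) = 0.0319
- z = (0.05 − 1.96 × 0.0321) / 0.0319 = −0.40, so power = 34.3%

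Nothing in this point changes it.

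**Step 3. What differential recording could do.** None of these inputs is in the documents:

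- True displacement is 50% in all groups.
- It is recorded in 95% of displaced fractures that were operated on.
- It is recorded in a share s of displaced fractures never operated on.
- An unrecorded displaced fracture is coded as undisplaced.

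Recorded prevalence = 0.50 × recording share. For operated patients this is 0.50 × 0.95 = 47.5%, with odds 0.475/0.525 = 0.905. The chance of p < 0.05 is for a two-proportion test with 118 per group.

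| s | Recorded, never operated | False gap (points) | False odds ratio | Chance of p < 0.05 |
|---|---|---|---|---|
| 60% | 30.0% | 17.5 | 0.905/(0.30/0.70) = 2.11 | 79% |
| 70% | 35.0% | 12.5 | 0.905/(0.35/0.65) = 1.68 | 50% |
| 80% | 40.0% | 7.5 | 0.905/(0.40/0.60) = 1.36 | 21% |
| 90% | 45.0% | 2.5 | 0.905/(0.45/0.55) = 1.11 | 6% |
| 95% | 47.5% | 0 | 1.00 | no bias |

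The gap and its significance column treat one group as wholly operated and the other as wholly never operated. The odds ratio also applies within the conservative group, where converted patients are the operated ones.

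If true displacement is varied from 30% to 70%, the false gap for s between 60% and 80% runs from 0.30 × (0.95 − 0.80) = 4.5 points to 0.70 × (0.95 − 0.60) = 24.5 points. At s = 90% it is 1.5 to 3.5 points.

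**Step 4. Sensitivity to the coding rule.** Suppose instead that unrecorded values are left missing and that recording does not depend on displacement itself. At a recording share of 60%, the displaced share among recorded patients is (0.50 × 0.60)/(0.50 × 0.60 + 0.50 × 0.60) = 50%. At 95% it is again 50%, and the odds ratio is 1.0. The bias in Step 3 therefore needs both unequal recording and the rule that silence means undisplaced, or some other link between being displaced and being recorded.

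**The case against.** The case on the other side is substantial, and most of it limits how far the point may be taken.

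- **A reader might infer that the presenting radiograph is not used at all.** The text does not say so. Delayed union and nonunion stand in the same record-extraction list and are nevertheless assessed on radiographs, so extraction from the record does not exclude looking at images. The record may also hold images, radiology reports or notes made at presentation, which Study Population requires within 48 hours of trauma. This stands. What remains is that image review is stated for the outcome and not for severity.
- **A reader might infer that severity is recorded more fully in operated patients.** No section describes completeness by treatment. It is a foreseeable risk, not a documented fact.
- **A reader might infer that the planned analyses are biased.** The primary comparison is an unadjusted chi-square test that does not use these variables. The failure regression names patient characteristics, which Recruitment lists apart from fracture characteristics. No adjustment or subgroup by displacement is announced, and the remark on displaced fractures reports a suggestion from prior work. This stands for the primary result. Descriptive reporting of the collected variables, and any later analytic use of them, would still inherit the problem.
- **The cohorts are mixed.** Study Design and Setting describes treatment as mainly, not wholly, conservative in one period and operative in the other. Any recording gap between the period cohorts would be smaller than between purely operated and purely never-operated patients. This stands.
- **The article is condensed, and the data form may say more.** This carries less weight, because the article is not silent: it names the source and the person for these items.

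**Conclusion.** The point holds in a limited form. As written, baseline dislocation and comminution come from manual record extraction by the researcher, although two surgeons already view every film and the outcome is read on radiographs. Recording may therefore differ by treatment and, within conservatively treated patients, by conversion to surgery. This could bias the description of the cohorts by severity and any regression or subgroup statement built on these variables.

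The primary chi-square test and the stated power are not affected. The size cannot be derived from the documents. It is zero if recording is equal, and the illustrative gaps and odds ratios above rest wholly on assumed recording shares and on coding unrecorded displacement as absent. To say that severity cannot be compared between the groups would go too far: the variables may not be comparable as collected, and the planned radiograph review offers a way to measure them uniformly. The change is worth making because it replaces a stated method with a less bias-prone one at little cost.

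**What to change.** Amend the Recruitment section so that:

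- the two trauma surgeons score dislocation, angulation and comminution on the presenting radiograph, with definitions set beforehand, during their existing identification review;
- they do so before later films or the patient record are opened;
- only these values serve as baseline severity in descriptive tables and in any regression or subgroup statement, and operation-report descriptions are not used for this purpose.

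The cost is a few extra fields on the review form and a little added reading time, with no new staff or imaging. The change is best made before the film review starts. The Results section reports that 2134 of about 2667 codes have been extracted but does not say whether films have been read, and any already read would need a second look. Once the surgeons know treatment and outcome, scoring without that knowledge becomes hard to achieve.

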### Outcomes

The primary outcome will be the delayed union and nonunion rates in the primary operative treatment group versus those in the conservative treatment group. The secondary outcomes will be the percentage of initial conservative treatment failure, which will be determined based on the percentage of patients who needed surgery after initially being treated conservatively; the number of patients who experience complications (infection and hardware failure); and associations between patient characteristics and failed initial conservative treatment. Functional outcomes—the complaints and impacts on daily living that are reported and experienced by patients—will also be secondary outcomes. These will be measured based on patients’ responses to the SF-12 and 3 categories (no more complaints or pain, minor complaints or pain without an impact on daily living, and significant complaints or pain with an impact on daily living).

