### Strengths and Limitations

Several limitations apply to our study. Since ours is a single-center study, included patients might not fully represent the general population when it comes to age, trauma mechanism, smoking status, and comorbidities. Although as much data as possible concerning baseline characteristics were retrieved, recollection bias could be an issue. Retrospective analyses do not allow for standardized follow-ups and the monitoring of outcome measures, such as fixed-term radiographs and final clinical recovery. However, we will be able to provide an overview of a large period of time to show possible differences in the outcomes of the two historic cohorts. Furthermore, as Dancer’s fractures are relatively rare, it would take several years to include a sufficient number of cases prospectively. With the use of a retrospective design, it is possible to gain a first insight into the outcomes of patients with Dancer’s fractures within a reasonable time frame.

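### The primary outcome counts only non-healing after 3 and 6 months, so a conservatively treated fracture operated on before 3 months and united by then scores as free of delayed union and nonunion

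*Protocol article*

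**What the plan says.** The protocol article, Recruitment, defines the events by time and radiograph: "Delayed union and nonunion are defined as absent or incomplete fracture healing after 3 and 6 months, respectively". Outcomes then sets the comparison: "The primary outcome will be the delayed union and nonunion rates in the primary operative treatment group versus those in the conservative treatment group". The groups in that sentence are named by initial treatment.

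Surgery after a conservative start appears in the same section as a secondary outcome, failure of initial conservative treatment, which is "determined based on the percentage of patients who needed surgery after initially being treated conservatively". No section says whether such surgery changes how the patient is scored for delayed union or nonunion.

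Two further statements bear on the scoring. Recruitment adds: "If patients are lost to follow up, it will be assumed that they did not experience delayed union, nonunion, or other complications". Strengths and Limitations concedes: "Retrospective analyses do not allow for standardized follow-ups and the monitoring of outcome measures, such as fixed-term radiographs".

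**The concern.** Surgery is the comparator, and it can remove the very event being counted. If a conservatively treated fracture is not healing, is operated on before 3 months and unites by 3 months, the union was obtained by surgery but is credited to conservative treatment. This route is specific to the conservative group, so the misclassification is one-sided.

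The stated hypothesis is that nonoperative treatment often leads to healing problems that primary surgery reduces. The masking works against that hypothesis and could help produce a null result that reflects the scoring rule. More than one paper is at stake: Future Directions makes a randomised trial conditional on promising results, and Sample Size proposes to use these data to size later studies.

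**Working it through.** **Step 1. Apply the definitions to each type of conversion.** All rows are patients who started conservatively and had surgery for impaired healing.

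| Course | Delayed union | Nonunion | Secondary surgery |
|---|---|---|---|
| Surgery before 3 months, united by 3 months | no | no | yes |
| Surgery before 3 months, not united at 3 months, united by 6 months | yes | no | yes |
| Surgery between 3 and 6 months, united by 6 months | yes | no | yes |
| Surgery before 6 months, still not united at 6 months | yes | yes | yes |

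Only the first row escapes the primary outcome completely. The second and third rows lose only the nonunion label. The fourth loses nothing.

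**Step 2. Reproduce the plan's power.** Inputs from Sample Size: 118 per group; conservative 3% to 9% in the general population; conservative 35% (delayed union) at age 40 and over; operative 4% to 7%. Alpha and sidedness are not stated, so two-sided 0.05 is assumed. With pooled variance under the null:

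Power = Φ{ [ |p1 − p2| − 1.96·√(2·p̄(1 − p̄)/n) ] / √( [p1(1 − p1) + p2(1 − p2)]/n ) }, where p̄ = (p1 + p2)/2.

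For 9% versus 4%: p̄ = 0.065; the null term is 1.96 × √(2 × 0.065 × 0.935/118) = 0.0629; the denominator is √((0.0819 + 0.0384)/118) = 0.0319. Power = Φ((0.05 − 0.0629)/0.0319) = 34.3%, as stated. For 35% versus 4% the result is 100.0%, and for 35% versus 7% it is 99.98%, consistent with the stated 100%. The plan's arithmetic is sound.

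**Step 3. Illustrate the masking.** Let f be the share of conservative failures converted and united before the reading that would have counted them. The observed conservative rate is p1 × (1 − f). The documents give no value for f, so every row with f above zero is an assumption.

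| True rates | f | Observed conservative | Difference (points) | Power |
|---|---|---|---|---|
| 9% vs 4% | 0 | 9.0% | 5.0 | 34.3% |
| 9% vs 4% | 10% | 8.1% | 4.1 | 26.1% |
| 9% vs 4% | 25% | 6.75% | 2.75 | 15.3% |
| 9% vs 4% | 50% | 4.5% | 0.5 | 3.8% |
| 35% vs 4% | 0 | 35% | 31 | 100.0% |
| 35% vs 4% | 25% | 26.25% | 22.25 | 99.8% |
| 35% vs 4% | 50% | 17.5% | 13.5 | about 92% |
| 35% vs 7% | 50% | 17.5% | 10.5 | 69.4% |

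At 9% versus 4%, f = 25% means 0.25 × 0.09 × 118 = 2.7 patients, so fewer than three reclassified patients more than halve the power. At 35% versus 4% the test survives heavy masking, but the estimate does not: 0.50 × 0.35 × 118 = 20.7 failures would be scored as healed.

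**The case against.** Several points on the other side are right and limit the finding.

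- A reader might infer that conservative failures in general drop out of the primary outcome. They do not. A patient operated on after 3 months for failure to heal has already met the delayed-union definition. Full escape needs surgery before 3 months and union by 3 months.
- A reader might take the Abstract's background as showing that masked conversions will be common. It describes secondary intervention as following delayed union and nonunion, and those patients are counted. Principal Results says a significant share of secondary surgery may be found, but gives no timing.
- A reader might infer that patients are counted twice, since every nonunion was also a delayed union. Rates at 3 and 6 months are ordinary cumulative reporting unless they are added together, and nothing says they will be.
- The 3 and 6 months are thresholds in a definition, not scheduled films; the article says fixed-term radiographs were not available.
- Conversions are not lost to the study. They are a named secondary outcome, and patients will be asked by telephone about secondary surgery in other hospitals.
- Healing under the initial strategy, later surgery included, is a legitimate quantity to estimate.

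The last two are the strongest, but they do not repair the primary comparison. Reporting conversions separately leaves the primary rate as low as before. The strategy quantity does not match the stated hypothesis about healing problems under nonoperative treatment, and the article does not say that it is what is wanted.

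**Conclusion.** The point holds as a gap in the primary outcome definition. A conservatively treated patient converted before 3 months and united by 3 months is scored as free of both events; one converted between 3 and 6 months and united by 6 months keeps the delayed-union label and loses only nonunion. If the conservative rate is truly the higher one, any such conversions bias the comparison towards no difference. The rule for patients lost to follow-up pushes the same way for someone who left and had surgery elsewhere, unless the telephone call reveals it.

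The size is unknown. The calculations rest on the article's own rates, 118 per group, two-sided 0.05 and an assumed masked share. They show sensitivity and do not predict the bias. The documents do not support a claim that the bias is large, that early conversion is frequent, or that the published power figures are wrong.

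**What to change.** Define one binary primary outcome per patient, attributed to the initial treatment: incomplete radiographic healing at 3 months, or secondary surgery for impaired healing before 3 months. Score nonunion in the same way at 6 months, as a secondary outcome. As a sensitivity analysis, report the radiographic-only outcome and the surgical component separately.

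The cost is a wording change and two extra data items, the date and the indication of secondary surgery. Recruitment does not list these explicitly, but the patient records are already being reviewed by hand, and the planned telephone call can supply them for surgery elsewhere.

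The downside should be stated in the plan. Secondary surgery depends on a decision as well as on the state of the bone, and the hospital's preference for surgery changed between the two periods, so the surgical component may differ between the cohorts for reasons other than healing. That is why the components need to be shown side by side. The change concerns scoring only and takes no view on when surgery should be done.
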